### Study population and recruitment

The CARES was constructed to detect rehabilitation needs and QOL, with a secondary intent to stimulate patients’ competences and patient empowerment for increased involvement in their own rehabilitation. Therefore, only patients with a primary cancer diagnosis treated with a curative intent will be recruited for this validation study. Details on the in- and exclusion criteria are listed in Table 4.

**Table 4 Tab4:** Inclusion and exclusion criteria for eligible patients

Inclusion criteria	Exclusion criteria
▪ Male and female cancer patients ▪ Primary stage I, II and III diagnosis ^a^ ▪ At different stages of the care process: recently diagnosed, currently undergoing treatment, and post-treatment in follow-up care. ▪ All types of cancer ▪ Aged between 25 and 60 years ^b^	▪ Having had or having premorbid neurological problems or cognitive dysfunctions ▪ The lack of proficiency in Flemish-Dutch

^a^ This criteria serves to exclude palliative patients, since we aim to include participants that have an perspective on rehabilitation

^b^ We believe the social context, role fulfillment, obligations and expectations differ between adolescents, adults and elderly resulting in other psychosocial concerns. To recruit adult cancer patients we chose the age range of 25–60 years

^c^ This makes a person unsuitable for participation in questionnaire research

Participants will be recruited from four Flemish hospitals (two public and two private, with a range from 340 to 1015 beds). In order to generate a representative research sample, several medical departments will conduct patient recruitment and include medical oncology, radiotherapy, gynecology, urology, and gastroenterology services.

### Study procedure

Eligible patients will be selected by the medical team according to the inclusion and exclusion criteria. Given the complexity of the clinical field and variable structures of the participating departments, two alternative procedures to invite patients to participate in the study will be used. On the basis of team organization and availability of time, the physician of the medical unit will choose to recruit patients with either the ‘face-to-face procedure’ or the ‘post procedure’. In the ‘face-to-face procedure’, a member of the medical team will explain the study briefly and invite the patient to participate. If the patient agrees to participate, he/she will immediately receive a study package with the informed consent form, a ‘what to do’-scheme, the first questionnaire and a stamped and addressed envelope to return the questionnaire. In the ‘post procedure’, eligible patients will be sent an identical study package by post, containing a short letter explaining the study, the informed consent form, a ‘what to do’-scheme, the first questionnaire and a stamped and addressed envelope to return the questionnaire. One week later participants have to fill in the second questionnaire, containing the CARES for test-retest reliability, and send it back in another stamped and addressed envelope provided. If the questionnaire is not sent back, the participants recruited via the ‘face-to-face procedures will be contacted by a team member and asked if they still want to participate and asked to return a completed questionnaire. Participants invited through post-procedure will be sent a reminder and second questionnaire package after 1 month. This study procedure is visualized in Fig. 1.

**Fig. 1 Fig1:**
[figure not shown]
Study procedure

Participants will be contacted by phone or by e-mail when returned questionnaires have a large number of missing responses or if the second questionnaire is not received in the expected timespan. Ethical standards limit the number of participant contacts, there is a maximum of two attempts to contact a participant.

### Questionnaires

Data collected with the *first questionnaire* includes socio-demographic characteristics, medical characteristics, the CARES and several concurrent instruments measuring the same concepts as the CARES or its subscales. These seven independent, but complementary, instruments are all considered to be international ‘gold standards’ or are frequently used instruments. These instruments were selected as they represent domains similar to the summary scales and global score of the CARES. All of them have been previously used in Belgian research. The concurrent validity of the original CARES was evaluated in comparison with the SCL-90, DAS and the KPS [34]. However, these instruments do not match the content of the CARES as completely as the set of concurrent measures in current study does. The concept equivalence and expected correlation with the CARES, to evaluate concurrent validity, is shown in Table 5.

**Table 5 Tab5:** Expected correlations of concurrent measures with CARES summary scales and global score

Summary scale and CARES global score	Concurrent instrument	Expected correlation^a^
Physical	KPS	-
Psychosocial	HADS-A HADS-D	+
Psychosocial	SSL-I SSL-D	- +
Marital	MMQ-M	-
Sexual	MMQ-S	-
CARES Global score	EORTC-QLQ -C30	-
CARES Global score	DT	+
CARES Needs	Care Needs Questionnaire E. Pauwels	+

^a^ ‘-‘= negative correlation, ‘+’ = positive correlation

*Abbreviations CARES* Cancer Rehabilitation Evaluation System, *KPS* Karnofsky Performance status Scale, *HADS* Hospital Anxiety and Depression Scale, *SSL-I* Social Support List – Interactions, *SSL-D* Social Support List – Discrepancies, *MMQ-M* Maudsley Marital Questionnaire – Marital, *MMQ-S* Maudsley Marital Questionnaire – Sexual, *EORTC-QLQ -C30* European Organisation of Research and Treatment for Cancer Quality of Life Questionnaire Core 30, *DT* Distress Thermometer

#### CARES [31–37]

The original CARES contains 139 items; however, not all 139 items apply to all patients and therefore patients complete a minimum of 93 items or a maximum of 132 items. Patients can rate each item, formulated as problem statement, on a 5-point Likert scale with zero representing “not at all” (no problem) and four representing “very much” (severe problem). The clinical form of the instrument that will be used in this study allows a patient to indicate which problems they believe require help, ticking ‘yes’ or ‘no’ on the question ‘Do you want help?’. Scores for the five summary scales can be computed as well as a CARES global score and an average severity score.

#### Karnofsky Performance status Scale (KPS) [48, 54, 55]

The KPS is an 11-point scale to judge the physical and daily functioning of a patient and ranges from 0 (completely dependent, not able to care for oneself) to 100 (fully active, not dependent and capable of normal activity without limitations). This measure is currently used worldwide in research and practice and has been administered for many years. The KPS has got good psychometric properties (interrater reliability: *r* = .97; concurrent validity: *p* < .001; predictive validity: *r* = .30).

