**Methods:**

After forward-backward translation of the CARES into Flemish we aim to recruit 150 adult cancer patients with a primary cancer diagnosis (stage I, II or III) for validation. In this study with a combination of qualitative and a quantitative approach, qualitative data will be collected through focus groups and supplemented by two phases of quantitative data collection: i) an initial patient survey containing questions on socio-demographic and medical data, the CARES and seven concurrent instruments; and ii) a second survey administered after 1 week containing the CARES and supplementary questions to explore their impressions on the content and the feasibility of the CARES.

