#### The European Organisation of Research and Treatment for Cancer Quality of Life Questionnaire Core 30 (EORTC-QLQ-C30) [66]

The EORTC QLQ-C30 is an internationally validated and widely used cancer-targeted QOL instrument, incorporating five functional scales (physical, role, cognitive, emotional and social) and three symptom scales (fatigue, pain and nausea, and vomiting). Items are answered on a 4-point Likert scale from 1 (‘not at all’) to 4 (‘very much’). The last two items on global health and QOL have 8-point answering scales ranging from 1 (‘very poor’) to 7 (‘excellent’). The EORTC QLQ -C30 is subject of a many validation studies worldwide, generally concluding the questionnaire is a QOL instrument with good psychometric properties relevant to different cancer-patient populations (internal consistency: α = .52–.92; test-retest reliability: *r* = .72–.84; scale inter-correlations: *r* = -.69–.85; responsive to change of health status).

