#### Care Needs questionnaire [70]

The Care Needs questionnaire was developed to assess the care needs of cancer survivors regarding relevant themes during reintegration: physical functioning, psychological functioning, self and body image, sexuality, relationship with partner, relationship with others and work and social security related aspects. For each theme, participants are asked whether they wish to receive information or support, in what way, when they prefer to receive information and support, and to what extent this need already has been met. Each of the questions are answered on 3- and 4-point Likert scales with different wording.

The *second questionnaire* contains a second CARES survey and specific supplementary questions to get data on participants’ experiences with the CARES. This second study component will be completed to assess test-retest and a patient-acceptability of the measure. Table 6 gives a detailed summary on the composition of both questionnaires and the measured concepts.

**Table 6 Tab6:** Composition of questionnaires for quantitative data collection

Questionnaires	Instrument	Data collected
*Questionnaire 1*		
*T* _*0*_ *Baseline*	Self-administered questions on socio-demographic and medical aspects	Age, sex, marital status, children, education, employment status, household income, social surrounding, involved care providers, diagnosis, date of diagnosis, treatment(s), start and end dates of treatments.
	CARES	Quality of life and rehabilitation needs
	KPS	Physical and daily functioning
	HADS	Symptoms of anxiety and depression
	SSL	Social support
	MMQ	Marital and sexual life adjustment
	EORTC-QOL-C30	Quality of life
	DT + PL	Distress and problems
	Care needs questionnaire administered by E. Pauwels	Care needs
*Questionnaire 2*		
*T* _*1*_ *After 1 week*	CARES	Quality of life and rehabilitation needs
	Self-administered questions	Relevance of CARES-topics, timespan filling in, mode preference,…

*Abbreviations CARES* Cancer Rehabilitation Evaluation System, *KPS* Karnofsky Performance status Scale, *HADS* Hospital Anxiety and Depression Scale, *SSL* Social Support List, *MMQ* Maudsley Marital Questionnaire, *EORTC-QLQ -C30* European Organisation of Research and Treatment for Cancer Quality of Life Questionnaire Core 30, *DT* Distress Thermometer, *PL* Problem List

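### Table 5 gives the 26-item CARES Physical scale one comparator, a single KPS rating, and does not pair it with the content-matched QLQ-C30 scales collected in the same questionnaire

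*Protocol article*

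**What the plan says.** Table 5 (section Questionnaires) gives the comparator and expected sign for each CARES score. The Physical row holds the KPS alone, with a negative sign. The QLQ-C30 appears once, in the row "CARES Global score EORTC-QLQ -C30", also negative, without saying which QLQ-C30 score is meant.

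The KPS section describes one rating from 0 to 100: "The KPS is an 11-point scale to judge the physical and daily functioning of a patient". The support cited there is "interrater reliability: *r* = .97; concurrent validity: *p* < .001; predictive validity: *r* = .30".

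On who completes it, the abstract describes "an initial patient survey containing questions on socio-demographic and medical data, the CARES and seven concurrent instruments". Under Study procedure, patients are handed or posted a package that includes "the first questionnaire and a stamped and addressed envelope to return the questionnaire". Table 6 lists the KPS in Questionnaire 1 ("KPS Physical and daily functioning") and names no rater.

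The QLQ-C30 section describes that instrument as "incorporating five functional scales (physical, role, cognitive, emotional and social"), plus symptom scales for fatigue, pain, and nausea and vomiting. Table 6 places it in Questionnaire 1 as well.

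The Concurrent validity section plans Spearman correlations by reference to Table 5. It labels absolute values below .30 low, .30 to .50 moderate, and .50 or more high.

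**The concern.** The Physical summary scale has 26 items on ambulation, daily living, recreation, weight loss, working, pain and clothing (Table 2). One overall performance rating is a coarse yardstick for that range. It may also be compressed at the top, because recruitment is limited to stage I to III patients aged 25 to 60 treated with curative intent.

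The cited reliability does not settle the matter. Interrater agreement shows that different raters score a patient alike; it does not show how dependable a patient's own rating is.

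What is at stake is interpretation. With the KPS as the only listed comparator, a modest correlation has two explanations that the listed analysis cannot separate: a weakness of the Flemish Physical scale, or a limitation of the KPS. The article says that unexpected psychometric results will be examined with the qualitative data, and that a negative evaluation can lead to changes in the instrument. An ambiguous result could therefore start a search for faults in the wrong place.

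**Working it through.** The plan states no figure to reproduce here. The check has a textual part and an illustrative part.

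**1. Content mapping (Table 2, Table 5, QLQ-C30 section)**

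| CARES Physical content | Closest QLQ-C30 scale collected | Paired in Table 5? |
|---|---|---|
| Ambulation, activities of daily living | Physical functioning | No |
| Difficulty working, recreational activities | Role functioning | No |
| Pain | Pain | No |
| Weight loss, clothing | None of the scales described | No |

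**2. Who rates the KPS**

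The abstract places the concurrent instruments in a patient survey. Study procedure has the patient receive the first questionnaire and mail it back, and describes no rating step by a clinician. Table 6 puts the KPS in that questionnaire. Self-completion is a strong inference, not a statement in the article. Of the three figures cited for the KPS, one is a reliability figure (interrater r = .97). The other two concern validity: a p-value and a predictive r of .30.

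**3. Ceiling (assumed inputs)**

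Inputs: the latent correlation between Physical and performance status is assumed, and so is the share of patients at the top KPS level. Neither is in the documents. Method: draw 400,000 bivariate normal pairs, cut the comparator into three to five ordered levels with the stated share in the top level, and take the Spearman correlation. Absolute values:

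| Latent correlation | No ceiling | 50% at top | 70% at top | 80% at top |
|---|---|---|---|---|
| .70 | .68 | .62 | .55 | .49 |
| .60 | .58 | .53 | .47 | .42 |

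At .70 the value falls below .50 only with about 80% at the top. At .60 it does so with 70%.

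**4. Unreliability of a self-rating (assumed inputs)**

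Formula: observed r = true r × √(KPS reliability × CARES Physical reliability). Assume a true r of .60 and a CARES Physical reliability of .90.

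- KPS reliability .97: .60 × √(.97 × .90) = .60 × .934 = .56
- .80: .60 × √.72 = .51
- .70: .60 × √.63 = .48
- .60: .60 × √.54 = .44
- .50: .60 × √.45 = .40

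**5. Precision at the target sample**

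For an observed Spearman of .50 and n = 150, the Bonett-Wright standard error on the Fisher scale is √((1 + .50²/2)/147) = √(1.125/147) = .0875. The interval is tanh(.549 ± 1.96 × .0875), about .36 to .62.

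**The case against.** A good deal can be said for the plan.

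- **The KPS is a relevant comparator.** By the article's own description it covers physical and daily functioning, and it was used in validating the original CARES. Keeping it for comparability is sound. A reader might infer that it is the least suitable measure available; that is wrong, since the HADS, SSL, MMQ and Distress Thermometer are further from this domain. Precedent is only a partial defence of using it alone, however. The article says that the original comparators match CARES content less completely than the present set, yet for Physical the listed comparator is still the KPS.
- **The QLQ-C30 is not left unused.** It is set against the Global score. The Concurrent validity sentence could also be read as every CARES score against every instrument. But that sentence defers to Table 5, which gives no expectation for Physical against any QLQ-C30 scale.
- **No pass mark is at risk.** Table 5 predicts only the sign, and .50 is a descriptive label. A correlation of -.49 would still agree with Table 5. This stands.
- **The attenuation figures depend on the inputs.** With an assumed latent .75, even 80% at the top leaves about .53. Table 4 admits recently diagnosed patients and patients under treatment, which may widen the KPS spread. At n = 150, a shift from just above to just below .50 lies within sampling error. This also stands.
- **The article may condense a fuller plan.** Subscale detail could sit in a document not shown. But Table 5 does fix a pairing for Physical, and the pairing it fixes is the narrow one.

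**Conclusion.** The point holds as an improvement to Table 5, not as an error that invalidates the analysis. On the text, the KPS is the only comparator listed for Physical, three content-matched QLQ-C30 scales from the same questionnaire are not assigned to it, and the one reliability figure cited for the KPS does not cover self-rating. That patients rate the KPS themselves is a strong inference.

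The size is conditional. Over the assumed range, a ceiling alone lowers the Spearman from .68 to between .62 and .49, or from .58 to between .53 and .42. A reader might infer that the validity verdict for Physical will be downgraded from high to moderate. The documents do not support that: they give no KPS distribution and no expected size of correlation, and they attach no decision to .50. What follows is narrower: a modest Physical-KPS correlation could not be put down to the Flemish scale rather than to the KPS.

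The effect is confined to concurrent validity for one summary scale. The sample size, reliability analyses and factor analysis are untouched.

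**What to change.** In the Physical row of Table 5, add three QLQ-C30 comparators beside the KPS: physical functioning (expected negative), role functioning (expected negative) and pain (expected positive). Keep the KPS for comparability with the original CARES validation. State who rates it and, if patients do, do not rely on the interrater figure as support for its reliability. Reporting the observed KPS distribution next to its correlation would show whether a ceiling is present.

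The cost is three more correlations on data already collected and an edit to Table 5 and the KPS description. No new data, patient burden or change in sample size is involved.

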#### The Hospital Anxiety and Depression Scale (HADS) [56–58]

The HADS was developed to identify symptoms of anxiety and depression in medically ill patients, and is used extensively in cancer patients and had excellent psychometric qualities. The questionnaire contains 14 items with four possible answers with scores ranging from 0 to 3. Higher scores on the two subscales (each consisting of seven items) indicate a higher level of anxiety or depression and the total score of the HADS (score-ranges from 0 to 42) can be used as a global measure of psychological distress. The HADS has got good psychometric properties (internal consistency: α = .67–.93; PCA: two factor solution; concurrent validity: *r* = .49–.83; subscale inter-correlations: *r* = .40–.74).

#### The Social Support List – Interactions and Discrepancies (SSL-I and –D) [59–61]

The SSL is a questionnaire with 75 items, 41 on experienced social interaction and 34 on experienced social discrepancies. In the first part of the questionnaire participants indicate how frequently certain social interactions occur on a 4-point Likert scale from 1 (‘seldom or never’) to 4 (‘very often’), with higher scores representing higher levels of social support. A second part of the SLL indicates the social discrepancies participants experience ranging from 1 (‘I would like it to happen more often’) to 4 (‘it happens too often’). Higher scores on the SSL-D indicate a greater lack of social support. The psychometric properties of the SSL are positively evaluated (internal consistency: α = .53–.93, test-retest reliability: *r* = .62–.85).

#### The Maudsley Marital Questionnaire (MMQ) [62–65]

The MMQ contains three scales exploring Marital (10 items), Sexual (five items) and General Life (five items) adjustment. The respondent is asked to indicate an answer from a series of possible answers, on a scale ranging from 0 to 8. The wording of response categories differ for each item depending on nature of the question. The MMQ has good psychometric properties (internal consistency: α = ..66–.90; PCA: three factor solution; subscale inter-correlations: *r* = .33–.60).

#### The European Organisation of Research and Treatment for Cancer Quality of Life Questionnaire Core 30 (EORTC-QLQ-C30) [66]

The EORTC QLQ-C30 is an internationally validated and widely used cancer-targeted QOL instrument, incorporating five functional scales (physical, role, cognitive, emotional and social) and three symptom scales (fatigue, pain and nausea, and vomiting). Items are answered on a 4-point Likert scale from 1 (‘not at all’) to 4 (‘very much’). The last two items on global health and QOL have 8-point answering scales ranging from 1 (‘very poor’) to 7 (‘excellent’). The EORTC QLQ -C30 is subject of a many validation studies worldwide, generally concluding the questionnaire is a QOL instrument with good psychometric properties relevant to different cancer-patient populations (internal consistency: α = .52–.92; test-retest reliability: *r* = .72–.84; scale inter-correlations: *r* = -.69–.85; responsive to change of health status).

#### The Distress Thermometer (DT) together with a Problem List (PL) [67–69]

Patients are asked to rate their overall distress on a visual analogue scale (presented as a thermometer) from 0 (‘no distress’) to 10 (‘extreme distress’). The DT is accompanied by the PL, which includes 35 items that address five life domains (practical, family/social, emotional, spiritual, and physical problems). Participants indicate if the topics of the items poses problems for them. At the end of the survey people are asked if they want to talk to a professional about their problems. The DT is frequently used in clinical practice and research all over the globe, in combination with the PL. This has proved to have good internal consistency (α = .80–.90).

#### Care Needs questionnaire [70]

The Care Needs questionnaire was developed to assess the care needs of cancer survivors regarding relevant themes during reintegration: physical functioning, psychological functioning, self and body image, sexuality, relationship with partner, relationship with others and work and social security related aspects. For each theme, participants are asked whether they wish to receive information or support, in what way, when they prefer to receive information and support, and to what extent this need already has been met. Each of the questions are answered on 3- and 4-point Likert scales with different wording.

The *second questionnaire* contains a second CARES survey and specific supplementary questions to get data on participants’ experiences with the CARES. This second study component will be completed to assess test-retest and a patient-acceptability of the measure. Table 6 gives a detailed summary on the composition of both questionnaires and the measured concepts.

**Table 6 Tab6:** Composition of questionnaires for quantitative data collection

Questionnaires	Instrument	Data collected
*Questionnaire 1*		
*T* _*0*_ *Baseline*	Self-administered questions on socio-demographic and medical aspects	Age, sex, marital status, children, education, employment status, household income, social surrounding, involved care providers, diagnosis, date of diagnosis, treatment(s), start and end dates of treatments.
	CARES	Quality of life and rehabilitation needs
	KPS	Physical and daily functioning
	HADS	Symptoms of anxiety and depression
	SSL	Social support
	MMQ	Marital and sexual life adjustment
	EORTC-QOL-C30	Quality of life
	DT + PL	Distress and problems
	Care needs questionnaire administered by E. Pauwels	Care needs
*Questionnaire 2*		
*T* _*1*_ *After 1 week*	CARES	Quality of life and rehabilitation needs
	Self-administered questions	Relevance of CARES-topics, timespan filling in, mode preference,…

*Abbreviations CARES* Cancer Rehabilitation Evaluation System, *KPS* Karnofsky Performance status Scale, *HADS* Hospital Anxiety and Depression Scale, *SSL* Social Support List, *MMQ* Maudsley Marital Questionnaire, *EORTC-QLQ -C30* European Organisation of Research and Treatment for Cancer Quality of Life Questionnaire Core 30, *DT* Distress Thermometer, *PL* Problem List

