As in all studies, this study has some limitations. Firstly, the completeness of the CARES content to assess QOL and supportive care needs should be considered. In comparison to other psychometric positively evaluated needs assessment tools for cancer patients, like the Supportive Care Needs Survey (SCNS) [76], the CARES does not include items on spiritual and existential well-being [29]. However, on other domains of well-being, we can judge in favor of the CARES content. The content of the CARES matches with our thoughts about the bio-psychosocial impact of cancer on patients’ lives and possibly resulting care needs. Furthermore, the content validity, completeness and feasibility of the CARES for Flemish cancer patients will be explored in the qualitative part of the larger study combining qualitative and quantitative methods. If the results of the study described in this research protocol result in a negative evaluation of the CARES’ psychometric properties, or it appears from the focus group discussions that there are deficits in the CARES content, formulation of items, or feasibility, adjustments for an improved Flemish version will be made. We plan to use this ‘final’ Flemish version in a pilot study where it will support the routine assessment and management of patients’ psychosocial concerns and needs in a clinical pathway with medical and psychosocial components. In the future, the instrument will also be made available for use in clinical practice.

Secondly, the use of two procedures to invite patients to participate in the study can introduce bias. An invitation to participate in research from a member of the medical team or by post could result in different response rates in both subgroups. This is a demanding study for patients and therefore also for professionals to convince patients to participate. Hence, some flexibility in the process of patient recruitment is needed. Some departments prefer a personal approach and want to invite their patients for the research personally, while others do not find the time in the clinical appointment to do this. Both procedures have been previously used in other validation research [66, 75, 77–80]. To assess any recruitment or consent bias, we will compare the data from the group of patients invited to participate in the hospital to the group invited by post.

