Thirdly, the questionnaire package composed with the CARES and several concurrent instruments asks for a time-investment of approximately an hour. This could present a burden to participants, resulting in discontinuation of participation. However, preliminary study results report approximately 58 % of the questionnaires distributed were returned completed. Eighty-four percent of the 153 participants who returned the first questionnaire also returned the second questionnaire completed.

Fourthly, the time between completing of the first and the second CARES survey could pose some problems. To examine test-retest reliability of an instrument the time period between two completions should be short enough to ensure that clinical change has not occurred, though long enough to prevent recall. While 1 or 2 weeks are recommended in literature [53], we ask participants to fill out the second questionnaire 1 week after the first. Preliminary results have shown some participants forget to fill in the second questionnaire or do not do so in a timely manner. They are reminded with a phone call by the researcher when de second questionnaire is not received in the recommended period of time. When data collection is completed, the time span between the two CARES-completions will be evaluated.

Fifthly, in earlier research the CARES was validated and used as a research tool for participants with various types of cancers, various cancer stages, at different phases of the care process, and often without age restrictions [31–44]. Because of the strict inclusion criteria we applied in our study, we have to state that the validation evidence from this study will not apply to patients above 60 years of age, and those with metastatic disease or in palliative care.”

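### Survey ratings of relevance, acceptability and completion time are asked only in questionnaire 2, so they cover only patients who returned a second CARES and may be biased upward

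*Protocol article*

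**What the plan says.** The abstract (Methods) describes "a second survey administered after 1 week containing the CARES and supplementary questions to explore their impressions on the content and the feasibility". In the Questionnaires section, the text that introduces the second questionnaire gives its purpose: "This second study component will be completed to assess test-retest and a patient-acceptability of the measure". Table 6 lists the data from its self-administered questions as "Relevance of CARES-topics, timespan filling in, mode preference", in a list left open with an ellipsis. All of this sits at T1, after one week and alongside a second full CARES. The questionnaire 1 rows of Table 6 contain no rating of the CARES.

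On retention, the Discussion (third limitation) reports: "Eighty-four percent of the 153 participants who returned the first questionnaire also returned the second questionnaire completed". On the one-hour package it says: "This could present a burden to participants, resulting in discontinuation of participation". The fourth limitation adds that "some participants forget to fill in the second questionnaire or do not do so in a timely manner".

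Feasibility has a second source. The Discussion (first limitation) states that "the content validity, completeness and feasibility of the CARES for Flemish cancer patients will be explored in the qualitative part of the larger study", and Design of the study plans focus groups for this purpose. The only comparison for recruitment or consent bias that the article states is between patients invited in hospital and those invited by post (Discussion, second limitation).

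**The concern.** The abstract makes later use of the Flemish CARES conditional on its being feasible as well as reliable and valid. The survey items that bear on feasibility reach a patient only if that patient goes on to a second questionnaire. Someone who found the CARES too long or irrelevant at T0, and stopped for that reason, is never asked. The chance of being observed may then depend on the quantity being measured, and the ratings would come from a group more tolerant of the instrument than those who first completed it.

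Test-retest reliability needs a second administration. A rating of a first completion does not, so the placement is a choice and not a necessity.

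Completion time raises a related question. If the item refers to the T1 completion, it describes patients who already know the form. If it refers to T0, it is recalled a week or more later. The article does not say which.

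**Working it through.** **Inputs from the article**
- First-questionnaire returners: 153 (Discussion, third limitation).
- Share of these who also returned a completed second questionnaire: 84% (same place).
- Placement of the rating items: questionnaire 2 only (Abstract; Table 6).

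**Inputs assumed, because the article gives no acceptability figure or threshold**
- pA, the share of questionnaire 2 returners who find the CARES acceptable: 90%, with 80% as an alternative.
- q, the same share among those who returned questionnaire 1 but not questionnaire 2: varied from 0 to 100%.

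**Step 1: the article's own figure.** 0.84 × 153 = 128.5. Both 128/153 = 83.7% and 129/153 = 84.3% round to 84%, so the figure is consistent with 128 or 129 raters. That leaves 153 − 129 = 24 or 153 − 128 = 25 patients who completed the CARES once and gave no rating.

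**Step 2: bias formula.** The rate among all 153 is 0.84 × pA + 0.16 × q. The survey reports pA. The bias is therefore pA − (0.84 × pA + 0.16 × q) = 0.16 × (pA − q).

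**Step 3: results with pA = 90%**

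| q | Rate among all 153 | Bias (points) |
|---|---|---|
| 0% | 75.6% | +14.4 |
| 50% | 83.6% | +6.4 |
| 75% | 87.6% | +2.4 |
| 90% | 90.0% | 0 |
| 100% | 91.6% | −1.6 |

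**Step 4: alternative with pA = 80%.** The bias runs from 0.16 × 0.80 = +12.8 points at q = 0 to 0.16 × (0.80 − 1) = −3.2 points at q = 100%.

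**Step 5: general limit.** Since pA − q cannot exceed 1, the bias relative to the 153 cannot exceed 16 points whatever the assumptions.

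**The case against.** The case against has several parts.

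- **Focus groups also assess feasibility.** Design of the study assigns content validity and feasibility to the qualitative arm, estimated at four or five groups of six to ten participants, and the Data analysis sections attach no threshold or test to the T1 items. This stands, and it limits the point to the survey ratings. A reader might infer that the whole feasibility conclusion rests on patients who completed the CARES twice; the article does not support that. Equally, it does not describe how focus group participants are chosen, so the groups cannot be assumed to include patients who stopped.
- **Burden is not the only explanation.** The burden sentence concerns the full package of CARES and concurrent instruments, and questionnaire 2 contains none of those instruments. Forgetting is a stated reason for missing or late second questionnaires, and late responders are contacted. This also stands. A reader might conclude that the ratings will certainly look too favourable; the documents support only that they may.
- **Timing of the completion-time item.** It is tempting to say that completion time will be understated through familiarity. Table 6 gives only a label, and the Conclusions foresee assessment throughout the care trajectory, so repeat completion is also an intended use. What remains is that the reported time cannot be interpreted until the completion it refers to is stated.
- **Reporting detail.** Denominators and responder comparisons are often left to an analysis plan or results paper. That is fair for the analysis, but the placement of the items is a design choice that the article itself fixes.
- **Late in the study.** With 153 first questionnaires already returned against a target of 150, moving the items would mainly help later administrations. This stands, and it is why the fix includes an analysis for data in hand.

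**Conclusion.** The point holds for the survey-based ratings. They are restricted to the 84% of 153 first-questionnaire returners who also returned a second CARES, and the article states no comparison of these patients with the other 16%. Upward bias is plausible, not certain. Its size is moderate: about 2 to 6 points if 90% of returners and 75% to 50% of non-returners find the CARES acceptable, 14.4 points at most with 90% among returners, and zero or slightly negative if non-returners rate it the same or better. All acceptability rates here are assumptions; only the 84% and the 153 come from the article.

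A reader might extend the argument to everyone who was given a package, using the reported return of about 58%. That would not be sound. Patients who never returned questionnaire 1 were not lost because of where these items sit, and moving the items would not recover them. The article also does not say outright that the 58% refers to questionnaire 1.

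This is a cheap improvement to evidence on a property that the adoption decision uses. It does not show that the feasibility conclusion will be wrong.

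**What to change.** **For any further administration**, such as the planned pilot: put the short relevance, acceptability and completion-time block in questionnaire 1, so that every T0 returner answers about a first completion. Mode preference and questions about repeat use can stay at T1. The cost is moving a few questions between two existing forms and a few extra minutes on a package that already takes about an hour.

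**For data already collected**:
1. Compare those who did and did not return questionnaire 2 on T0 item non-response, distress (Distress Thermometer, HADS) and CARES scores.
2. Report acceptability among questionnaire 2 returners together with best- and worst-case bounds over all 153, counting the missing 24 or 25 first as all acceptable and then as all not acceptable.
3. State which completion the reported time refers to.

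These steps need no new data, only a comparison of baseline variables already in hand, a second denominator and a label.
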